### Randomisation

The study will be a randomised controlled trial, with a one-year follow-up period. Practices are stratified according to practice size as solo, duo, or group practice. On inclusion, practices are assigned to one of the study groups using randomisation in blocks of four per stratum by a research assistant. Blocks were generated electronically with the help of a statistician. The randomising procedure itself is concealed for practices, consultants, and researchers ([name], MW). The regional advisors including the practices have no access to the randomisation process. After randomisation, both the practice and the regional advisor are informed. The intervention is open to all involved.

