## Methods

The project will be a collaborative project of IQ healthcare, a research department of Radboud University Nijmegen Medical Centre, and the four regional supportive structures for primary care ('ROS') in the south of the Netherlands and their cooperative bond Robuust. The medical ethical committee (CMO Regio Arnhem -- Nijmegen) assessed the study proposal and waived approval.

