### Participants

The study population will consist of 60 general practitioners (GPs) and the CHF patients they will include. GPs will be recruited in the south of the Netherlands, contacted either directly or indirectly via various regional organisations by advisors of the regional supportive structures for primary care. GPs will be informed about the project, and when they agree to participate they will be instructed to send in an admission form with data on practice organization necessary for stratification and randomization.

Evidence of change will be assessed by studying the effects of the intervention on patients with CHF registered with the participating GPs. As in the pilot [10], GPs will include all CHF patients from their practices who are over 18 years of age of whom the GPs consider themselves to be the physician taking care of the treatment of this condition in the patient. We expect eight to ten patients per practice [18,19]. Patients will be sent explanation about the study and asked for informed consent to participate in a patient questionnaire. Data collection will be anonymized.

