### Time frame

Practice inclusion is planned from June until October 2010. After inclusion, practices participate in the programme during one year. At the start of the year, the GPs include all their patients with CHF they treat at least in part themselves. During that year, patients with newly diagnosed CHF can also be included. Data management in the patient registration forms is a continuous process during the project year. After the project period of a year, the forms are anonymised and sent to the researchers coded. Furthermore, practices will send coded patient questionnaires with explanation of the survey and ask for an informed consent; these will be returned to the researchers. Finally the researchers will contact the GPs participating for the telephone interview. The GPs will receive feedback based on the patient registration forms and the questionnaires.

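### Fixed blocks of four, with each result told to the recruiting advisor while recruitment is open, leave later allocations open to prediction despite the stated concealment

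*Protocol article*

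**What the plan says.** The Randomisation section of the protocol article sets the procedure: "On inclusion, practices are assigned to one of the study groups using randomisation in blocks of four per stratum by a research assistant". It defines the strata: "Practices are stratified according to practice size as solo, duo, or group practice". On concealment it says: "The randomising procedure itself is concealed for practices, consultants, and researchers", and it adds that the regional advisors who include practices cannot access the process. It then says: "After randomisation, both the practice and the regional advisor are informed. The intervention is open to all involved".

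Three other sections bear on the point:

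- **Participants:** GPs are "contacted either directly or indirectly via various regional organisations by advisors of the regional supportive structures for primary care". A GP who agrees sends in an admission form with the data needed for stratification and randomisation.
- **Time frame:** "Practice inclusion is planned from June until October 2010".
- **Methods (opening paragraph):** the project partners include "the four regional supportive structures for primary care ('ROS') in the south of the Netherlands" and their joint cooperative body.

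The abstract repeats the block size of four. The article mentions no variation in block size and no delay before the advisor is told.

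**The concern.** Concealing a list and making the next assignment unpredictable are different things. When assignment follows inclusion one practice at a time, the block size is fixed and small, and results are released as they arise, past results carry information about the next one. Two like results at the start of a block settle the other two, and the fourth place is always settled by the first three. No access to the list is needed. Here the results go to people with a recruiting role, during a recruitment period of about five months, in an open trial.

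An advisor who could foresee the next arm could influence which practices are approached and when. More motivated practices, or those better organised for CHF care, could then gather in one arm.

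The design has little protection against that. The Data analysis section makes the primary analysis a comparison at follow-up. The Discussion says that the patient questionnaire is measured once, at the end. PACIC and EQ-5D, two of the three primary outcomes, therefore have no baseline against which to see or adjust an imbalance. The target difference on PACIC is 0.3 points with a standard deviation of 1, so modest selection could matter.

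**Working it through.** **Plan's own figures.** The article gives no figure for predictability. Its sample size is not in question and reproduces. With two-sided alpha 0.05 (sidedness assumed) and power 0.80, n per arm is 2 × (1.960 + 0.842)² / 0.3² ≈ 174.4. With 10 patients per practice, 2 × 174.4 × 1.45 / 10 = 50.6, so 51 practices. With 8 patients, 2 × 174.4 × 1.35 / 8 = 58.9, so 59 practices.

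**Inputs from the article.** Block size four, three strata, assignment on inclusion and results told to the advisor (Randomisation); four regional structures (Methods); 60 GPs (Participants).

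**Assumptions.** 1:1 allocation, so each block holds two practices per arm (2:2); 60 GPs taken as 60 practices; regions and strata of equal size; random order of arrival; the advisor knows the block size and the position in the block.

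**Step 1: all earlier results in the stratum known.** There are 6 equally likely orderings of AABB.

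- Chance that the allocation is certain, places 1 to 4: 0, 0, 1/3, 1. Average: (1/3 + 1) / 4 = 33.3%.
- Chance that the best guess is right (name the arm with more places left): 1/2, 2/3, 2/3, 1. Average: (1/2 + 2/3 + 2/3 + 1) / 4 = 70.8%.

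**Step 2: each earlier result known with probability p.** Write q = 1 − p.

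- Third place: certain if both earlier results are known and alike, p² × 1/3.
- Fourth place: certain if all three are known (p³), or if exactly two are known and alike (3p²q × 1/3 = p²q). The sum is p².
- Share certain: (p²/3 + p²) / 4 = p²/3.
- Best guess by place: 1/2; 1/2 + p/6; 1/2 + (1 − q²)/6; q³/2 + 2pq + p³.

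| Knowledge | p | Certain | Best guess right |
|---|---|---|---|
| Own region only, four equal regions | 1/4 | 1/48 = 2.1% | (0.500 + 0.542 + 0.573 + 0.602) / 4 = 55.4% |
| Half of the results | 1/2 | 1/12 = 8.3% | (0.500 + 0.583 + 0.625 + 0.688) / 4 = 59.9% |
| All results pooled | 1 | 1/3 = 33.3% | 70.8% |

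**Step 3: cross-check by simulation.** Simulating 60 practices in three strata, where the last block in a stratum may be incomplete, gave 31% certain and 70% right with everything pooled; 8% and 60% with two regions; 2% and 55% with four; 0.5% and 53% with eight separate advisors.

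**Step 4: what varying block sizes would do.** Guessing the arm that is behind needs no knowledge of block size. The expected number of correct guesses in a block of 2b is b + 2^(2b−1)/C(2b,b) − 1/2. For a block of four this is 2 + 8/6 − 0.5 = 2.833; for a block of six it is 3 + 32/20 − 0.5 = 4.1. With sizes 4 and 6 equally likely, the rate is (2.833 + 4.1) / 10 = 69.3%, against 70.8% for fixed fours. Certainty falls much more, because two like results no longer settle the rest if the block might be a six.

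**The case against.** A reader might infer that advisors can often work out the next allocation and that the stated concealment has failed. The article does not support that.

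- The 33% and 71% figures need a known block size and every earlier result in the stratum. The article does not say that advisors have either, and the block size may be part of what is withheld from them.
- In "After randomisation, both the practice and the regional advisor are informed" the advisor is singular, most naturally the one for that practice. Blocks run by practice size and not by region, so own results are a thin sample of each block. Even the 2% figure needs the position in the block, which means counting other regions' inclusions.
- A reader might also infer that advisors can hold back an admission form. In the Participants section it is the GP who sends it, after agreeing and before randomisation. Contact can also run through other organisations. What is left to the advisor is whom to approach and when.
- No motive is shown. Both arms receive the programme with three practice visits, and partnership in the project does not imply a favoured arm. Predictability is not bias, and no bias in PACIC has been estimated.
- An imbalance would not be wholly invisible. The registration forms record treatment at patient inclusion, admission forms give practice data, and practice size is stratified and modelled.

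All of this stands, and it sets the size of the point. It does not remove it. The 2% is not a guaranteed value either: it assumes equal regions, evenly spread over strata, that exchange nothing. The regional structures share a cooperative body, and a region that supplies half of a stratum would be nearer 8% and 60%. The registration forms are an indirect check on PACIC and EQ-5D, and practices complete them after they know their arm.

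**Conclusion.** The point holds as a design weakness that the text leaves open. It is not a demonstrated breach of concealment. The article itself fixes the mechanism: assignment on inclusion, one block size of four, visible strata, and results fed back to recruiting advisors during recruitment. Lack of access to the list does not prevent inference from past results.

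With 2:2 blocks and a known block size and position, the range runs from about 2% certain and 55% guessed right (own results only, four equal regions) to at most about 33% and 71% (all results pooled). Where the trial would fall depends on information flow that the article neither describes nor limits. Without knowledge of block size or position, the figures for certainty are lower still. Confidence is high that the mechanism is present and moderate at best on how often prediction would succeed. No figure in the article changes. The point merits action because two primary outcomes lack a baseline and the remedy is cheap.

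**What to change.** Make one of these the main change:

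- **Withhold results.** Tell the practice and its practice visitor, but not the recruiting advisors, until recruitment closes. Because the trial is open and advisors work locally with practices, some results may still leak.
- **Allocate in batches.** Randomise within stratum after a set of admission forms is in, in random order within the batch. This depends less on secrecy. For scale, 60 practices over five months and three equal strata average 60 / (5 × 3) = 4 per stratum per month, about one block.

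In addition, use randomly varying block sizes (for example 4 and 6) within each stratum and do not disclose them to recruiters. Alone this is not enough: it removes most certainty but lowers the best-guess rate only from 70.8% to 69.3%.

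The cost is a regenerated electronic list and a changed notification rule. Advisors learn allocations later, practices may wait for a batch (up to about a month if monthly), and arm sizes within a stratum may differ slightly more. Strata, outcomes and sample size stay as they are.

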### Data analysis

The primary analysis is a comparison of primary outcomes at follow-up between the study groups, taking into account clustering of patients within practices. Multilevel regression analyses will be used to explore the effect of practice size and type of intervention programme. In addition, we will examine both changes within groups and differences at follow-up between groups with respect to percentage of patients on the maximum tolerated dosage of ACE inhibitor or angiotensin II receptor blocker and of beta blockage; medication completely according to the guideline; having received influenza vaccination in the winter season 2010-2011; having received professionally guided physical activity training; and the number of non-pharmaceutical issues addressed. If possible, subgroup analyses will comprise type of CHF (systolic or diastolic) and diagnostic certainty (secondary care diagnosis, echocardiography diagnosis) The interviews will be used to assess the feasibility of the programme and goal attainment, organisational changes in CHF care, and formalised cooperation with other primary care disciplines and specialist care.

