### Measures

Data collection will comprise the following measures: patient questionnaires, patient registration forms, and telephone interviews with the GPs. Practices will send out patient questionnaires based on validated and previous used questionnaires: PACIC [21], EQ-5D [22], questions about 'continuity of care,' and Morisky's questionnaire on medication adherence [23]. In the patient registration forms, data about non-pharmaceutical and drug therapy are registered by the GPs and their staff: they register the baseline treatment at inclusion, and during the patient contacts throughout the study period they register all advice given, referrals, drug therapy changes, and information on hospitalisation and mortality. The GP interview will score goal attainment and a qualitative assessment of the programme. All measures have been applied by our group in previous studies.

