### Outcomes

The primary outcome measures are determined at the patients' level and consist of experience of receiving structured primary care for CHF (PACIC) and health-related utilities (EQ-5D), and of drug prescriptions.

PACIC is a questionnaire consisting of 27 items, which is related to the Chronic Care Model [24]. We translated and validated PACIC for use in general practice in the Netherlands [25]. EQ-5D consists of five questions and a Visual Analogue Scale (VAS), which has been validated for use in the Netherlands [26]. These outcome measures reflect key aspects of medical treatment, organization of care, and patient reported quality of life, and were chosen pragmatically because of the availability of relevant, validated, responsive, composite measures.

Drug prescription scores are assessed using the guideline adherence index (GAI), indicating the proportion of indicated drugs that is prescribed [27,28]. These include ACE inhibitors and beta blockers, and -- depending on the patient's CHF severity according to the NYHA classes -- further drug classes [12].

Secondary outcome measures at the patients' level concern lifestyle advice and medication during the study period, based on the patient registration forms providing information on non-pharmaceutical advice and drug prescriptions, continuity of care, and medication adherence. Considering drug therapy we will assess the percentages of ACE inhibitors and beta blockers prescribed in the evidence-based target dosages. Secondary outcome measures at the practice level are goal attainment and qualitative assessment of the programme, focussing on the subjective GP's experiences, for instance on improvement of practice organisation and collaboration with other primary care professionals.

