## Discussion

There exist various classifications of barriers (and facilitators) and multiple approaches for linking interventions to barriers [29-31]. In their systematic review, Légaré and colleagues propose a conceptual framework with knowledge, attitude, and behaviour as main factors [31]. Our choice of barriers is based on a list rigorously developed in the Netherlands with a literature study in 2002, expert input, and tested in various projects in the Netherlands [20]. Our main factors for ordering the barriers are related to the innovation, the healthcare professional, the patient, and the context. The barriers presented in this study correspond very well to the barriers found most often in the Légaré review, including time pressure and lack of applicability. Looking for the barriers for each individual practice and not for the practices participating in general, we decided to have the barriers proposed scored in email contact with the GPs in two rounds.

Several studies were conducted to assess the effect of tailoring implementation. In a systematic review, the authors conclude that identifying barriers and tailoring intervention to these barriers may improve clinical practice compared to no intervention and to guideline dissemination. In their meta analysis including eight studies identified with a non-tailored intervention in the control group, they report a modest effect of tailoring [13].

All data collection will take place at the end of the project period. Within the context of the evaluation of the implementation project, it is not feasible to have data collection both at the start and at the end, but the patient registration form will have baseline data on treatment issues. This also will allow for within group analyses, giving information about the effectiveness of both implementation strategies separately. Unfortunately, this data collection, either paper based or electronically, will require additional administrative actions from the practices. Enabling data collection from the electronic medical record will be beyond the scope of this project. Considering the patient questionnaire's results, with one measurement at the end, this restricts us to intergroup analyses.

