Our sample size is based on power calculation considering the PACIC outcomes. In previous research, a difference of 0.5 was found in the evaluation of a CHF and a diabetes programme [32,33]. Thus, an effect size of 0.3 on PACIC can be considered a modest effect. We aim at a lowered effect because we compare two strategies that are both to be expected to have some impact.

Drug prescription is also a primary outcome measure. We will present the GAI as a measure for the percentage of indicated drugs prescribed. In previous research, many patients appeared to receive suboptimal dosages. When considering ACE inhibitors and beta blockers, we will report on the percentage of prescriptions in the indicated, high-target dosages [34].

We decided to stratify practices included based on practice size. There is some evidence of a relation between practice size and quality of care [35,37]. In one study, larger practice size was associated with more structured care [35]. Stratification of practices based on practice size could be defined as the number of GPs in the practice and based on patient list size. We choose a stratification scheme based on the former, with the strata solo, duo, and group practices, which appeared feasible in previous research leading to strata of comparable size.

CHF patients do not form a homogeneous group; apart from aetiology, we make a distinction between systolic CHF and CHF with preserved left ventricular function (diastolic CHF). In our study, both patient groups may be included, as the practice guideline gives recommendations for both the patients with and without left ventricular systolic dysfunction. Subgroup analyses will be performed.

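### The between-arm comparison of the guideline adherence index (GAI) is stated on follow-up values only, although baseline drug treatment is recorded and could be adjusted for

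*Protocol article*

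**What the plan says.** The Data analysis section of the protocol article sets one rule for the primary outcomes: "The primary analysis is a comparison of primary outcomes at follow-up between the study groups, taking into account clustering of patients within practices". It continues: "Multilevel regression analyses will be used to explore the effect of practice size and type of intervention programme". No baseline covariate is mentioned.

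The Outcomes section names three primary outcomes: PACIC, EQ-5D and drug prescriptions. The last is scored as follows: "Drug prescription scores are assessed using the guideline adherence index (GAI), indicating the proportion of indicated drugs that is prescribed".

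The three differ in what is measured at the start:

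- **PACIC and EQ-5D.** The Discussion is open about the limit: "Considering the patient questionnaire's results, with one measurement at the end, this restricts us to intergroup analyses".
- **Drug treatment.** The Measures section says of GPs and their staff that "they register the baseline treatment at inclusion". The Discussion confirms that "the patient registration form will have baseline data on treatment issues". The section on standardised delivery also lists drug treatment at the start of the project among the items collected.

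The Discussion names one use for these baseline data: "This also will allow for within group analyses, giving information about the effectiveness of both implementation strategies separately". For other drug and advice measures, the Data analysis section plans within-group changes and between-group differences at follow-up, as two separate things.

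**The concern.** A rule that is unavoidable for two outcomes has been extended to a third that does not need it. The null hypothesis concerns tailored against standardised delivery. A before-after change within one arm does not test that; a between-arm comparison adjusted for baseline does. As written, the baseline drug data serve the weaker purpose and are not named for the stronger one.

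Prescribing for a chronic condition tends to persist, so baseline GAI is likely to predict follow-up GAI. Without adjustment, differences that predate randomisation stay in the error term. Any chance imbalance between the arms also passes into the estimate. This matters more here because the Discussion expects a modest contrast between two active strategies, and the sample size was set for PACIC, not the GAI.

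**Working it through.** **1. The plan's own figure.** Inputs from the Sample size section: difference 0.3, SD 1.0, alpha 0.05 (two-sided reproduces), power 0.80, ICC 0.05.

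- Per arm before clustering: 2 × (1.960 + 0.842)² / 0.3² = 174.4.
- Design effect 1 + (m − 1) × 0.05: 1.45 for m = 10 and 1.35 for m = 8.
- Practices: 2 × 174.4 × 1.45 / 10 = 50.6, so 51; and 2 × 174.4 × 1.35 / 8 = 58.9, so 59.

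Both stated numbers reproduce. The power calculation is not in error.

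**2. Assumptions for the GAI.** The documents give no SD, ICC or baseline-to-follow-up correlation r for the GAI. I work in SD units, borrow the PACIC ICC of 0.05, take 60 practices split equally with 8 or 10 patients each, and vary r. The effective number per arm is 30 × 8 / 1.35 = 177.8 or 30 × 10 / 1.45 = 206.9.

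**3. Chance imbalance at baseline.** The SE of the between-arm difference in mean baseline GAI is √(2 / 177.8) = 0.106 SD or √(2 / 206.9) = 0.098 SD. The 95% range is about ±0.21 or ±0.19 SD. With equal SDs at both times, a fraction r of an imbalance carries into the follow-up difference. An imbalance of 0.21 SD would shift it by 0.5 × 0.21 ≈ 0.10 SD at r = 0.5, or 0.8 × 0.21 ≈ 0.17 SD at r = 0.8.

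**4. Gain from adjustment.** With the same r at patient and practice level, the variance of the effect is multiplied by 1 − r². The detectable difference at 80% power is (1.960 + 0.842) × √((1 − r²) × 2 / n), with n the effective number per arm. The last column uses an illustrative effect of 0.2 SD, since the article gives no target for the GAI.

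| r (assumed) | Variance left | Detectable difference, SD (8 / 10 patients) | Power for 0.2 SD (8 / 10 patients) |
|---|---|---|---|
| no adjustment | 100% | 0.297 / 0.275 | 47% / 53% |
| 0.3 | 91% | 0.283 / 0.263 | 51% / 57% |
| 0.5 | 75% | 0.257 / 0.239 | 59% / 65% |
| 0.7 | 51% | 0.212 / 0.197 | 75% / 81% |
| 0.8 | 36% | 0.178 / 0.165 | 88% / 92% |

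**5. Sensitivity to unequal correlations.** With rc at practice level and ri at patient level, the factor is [0.05(1 − rc²) + 0.95(1 − ri²)/m] / [0.05 + 0.95/m].

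- ri = 0.5, rc = 0.8: 63% left (m = 8) or 62% (m = 10).
- ri = 0.8, rc = 0.5: 48% or 49% left.

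**6. Sensitivity to uninformative baselines.** If a share q of patients has none, roughly 1 − (1 − q)r² is left. For q = 20% (assumed): 80% at r = 0.5, 61% at r = 0.7 and 49% at r = 0.8.

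**The case against.** The strongest reply is that this is a condensed article, and covariates are usually listed in an analysis plan that is not shown. A comparison at follow-up may simply name the time point, and a model adjusted for baseline would fit those words. The article says baseline data also permit within-group analyses, which does not exclude other uses. This lowers the weight of the point. It does not remove it: the article defines the primary comparison, says what the baseline data are for, and does not connect the two.

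Several further objections stand and limit the point:

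- **Practice size.** A reader might infer that the stratification factor is left out of the primary model, especially since the Discussion reports that in one study "larger practice size was associated with more structured care". The text does not show this. Practice size is named beside programme type in the same regression sentence, so the natural reading is that both are terms. It only needs to be made explicit.
- **Availability of baseline.** Recording it for every patient is the plan, not a certainty. Practice staff complete the forms, newly diagnosed patients may enter during the year (Time frame), and some indications within the GAI depend on NYHA class, which the article's description of the form does not list.
- **Selective inclusion.** GPs include patients after their practice has been assigned, and the intervention is open. Adjusting for baseline GAI does not cure that.
- **Logistics.** Asking practices to send the baseline page to the researchers at inclusion would conflict with the Time frame and Discussion, which place collection at the end and call collection at both ends infeasible. It is not proposed here.

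**Conclusion.** The point holds for the GAI and for other registration-form outcomes that have a baseline. It concerns efficiency and conditional imbalance, not validity: leaving selective inclusion aside, comparing randomised practices at follow-up is unbiased in expectation. Adjustment would remove about 25% of the variance at r = 0.5, 49% at r = 0.7 and 64% at r = 0.8. These values of r are assumptions, taken as equal at both levels; the documents give none.

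Two stronger readings are not supported. A reader might infer that most of the available precision is lost, but that needs r above 0.71, and more if some baselines are uninformative. A reader might also extend the criticism to the primary analysis as a whole, but PACIC and EQ-5D have no baseline and the article explains why. The amendment is worth making because the data are already being collected.

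**What to change.** Specify the primary GAI comparison as a multilevel regression of follow-up GAI on arm, baseline GAI and practice-size stratum (solo, duo, group), with a random practice effect. State in advance a simple rule for patients whose baseline is missing or uninformative, such as those newly diagnosed during the year.

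Use the same form for other registration-form outcomes that have a baseline. For yes/no outcomes this means the logistic counterpart, to which the variance figures above do not carry over directly.

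State that the practice-size stratum is a term in the PACIC and EQ-5D models, and otherwise keep those follow-up only.

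The cost is a few sentences of analysis text and the handling of missing baselines. No new data, visits or forms are needed.
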